**Methods:**

The study will be conducted with adult male patients with SUD at a rehabilitation center and control volunteers. Participants will undergo a self-reported demographic and psychological assessment, a clinician-administered craving and emotional reaction test, and will also be monitored using a smartwatch. SUD participants will be monitored for a total of 18 months (6 months during rehabilitation, an additional 12 months post discharge), and control participants for a total of 6 months. All participants will be reassessed at the sixth month of monitoring. The collected data will then be used to train models with a neural network, which will then be validated against other models and compared with other algorithms. Demographic, psychological, digital biomarkers, and craving profiles will be created, correlations will be analyzed, and they will be compared with controls to generate a digital phenotype of SUD. When the model achieves adequate validity (area under the curve of ≥0.80), a graphic user interface will then be designed for clinical use.

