Machine learning (ML) has also been used as a tool for the diagnosis of anxiety disorders with the use of speaking patterns, gaming activities, and self-reports [40-49]. It has also allowed researchers to measure the severity and variability of that disorder in varying environments through wearables, allowing remote intervention and through simulations [30,48,50-52]. It has also been used in predictive models for early depression diagnosis through smartphone use, severity, and progression through physical activity, sleep, and social interaction data [53-61]. In addition, ML models (MLM) have been trained to detect relapse in MDD and risk of suicide [62-64]. Similarly, it has been used to predict the start of a psychotic episode 5 days before it by using patterns of movement and sleep disturbance [63,65].

With a 60% relapse rate, an average of 5 recovery attempts required for full remission, and a growing number of new patients with SUD presenting at younger ages [2], this disorder represents a significant opportunity for digital health technologies. These tools, often used in managing cognitive and mood disorders commonly comorbid with SUD, have the potential to enhance treatment effectiveness and reduce relapse rates.

This study aims to integrate physiological, behavioral, and psychological data through digital technologies to develop comprehensive digital profiles of individuals with SUD. These profiles will be analyzed using ML tools to identify clinically relevant patterns. The resulting models are intended to serve as complementary tools in clinical practice, supporting treatment decisions, improving prognostic accuracy, and facilitating the monitoring of patients in remission.

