### Data Preprocessing

Databases and labeling will initially be managed using Microsoft Excel (version 2412), after which MATLAB (version 2025a, MathWorks, Inc) will be used for data preprocessing. This process will include data cleaning and preparation to ensure the dataset is suitable for ML training.

Feature selection will be done following a filter methodology after correlation analysis to assess the correlation with the target and statistical measures. All data obtained through the wearable device, psychological assessment and ESDC will be scaled through a *z*-score standardization for dimensionality reduction and integration across all modality.

The data will be divided into training, validation, and test datasets using a k-fold cross-validation approach. The dataset will be split into k folds, with 2 folds randomly selected: one for validation and another for testing. The remaining k-2 folds will be used for training. The number of folds will vary depending on the specific model, enabling a broader experimental variance and improved model evaluation.

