### Validation and Verification

All models and algorithms will undergo validation, verification, and testing using MATLAB’s tools for model evaluation and hyperparameter optimization. These processes will assess precision, performance, and recall metrics. Optimal model performance will be defined by achieving an area under the curve (AUC) of ≥0.80 and F2 score of ≥0.8.

The output categories will serve as benchmarks to evaluate the validity, reliability, and precision of the models. The validation dataset will be used to perform initial comparisons both within individual models of each algorithm and across different algorithms, replicating models with distinct architectures to refine performance.

For model verification, the test dataset will be used to determine final AUC and F2 scores. This final evaluation will confirm the models’ effectiveness as ML tools for predicting rehabilitation outcomes and informing clinical decision-making.

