#### Predictive Model

A predictive model will be developed to distinguish between healthy individuals and patients with SUD. In addition, the model will predict the duration of a rehabilitation therapeutic program and the length of sobriety adherence for individuals rehabilitated using the center’s methodology. A minimum performance threshold of AUC≥0.8 and F2≥0.8 has been established to evaluate the model as fully functional.

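### At the planned minimum size, the success rule (AUC ≥0.80 and F2 ≥0.8) separates useful from useless models poorly

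*Protocol article*

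**What the plan says.** In the protocol article, Validation and Verification sets the criterion: "Optimal model performance will be defined by achieving an area under the curve (AUC) of ≥0.80 and F2 score of ≥0.8". Under Outcomes, Predictive Model repeats it as the bar for use: "A minimum performance threshold of AUC≥0.8 and F2≥0.8 has been established to evaluate the model as fully functional". The Discussion (Principal Findings) makes the same pair the test of the study hypothesis.

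The abstract differs. Its Methods paragraph has AUC alone as the trigger for the clinical interface: "When the model achieves adequate validity (area under the curve of ≥0.80), a graphic user interface will then be designed for clinical use".

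On where the numbers come from, Validation and Verification says that "the test dataset will be used to determine final AUC and F2 scores". Data Preprocessing describes that dataset: "The dataset will be split into k folds, with 2 folds randomly selected: one for validation and another for testing". It adds that "The number of folds will vary depending on the specific model", so k is not fixed.

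Sample Size sets a minimum of 25 per group at a 1:1 ratio and aims for more. Output defines two labels for duration of therapy and three for relapse latency. No positive class or averaging method is given for F2. The only relapse frequency in the article is a background figure in the Introduction: "With a 60% relapse rate, an average of 5 recovery attempts required for full remission".

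**The concern.** This pair of thresholds is the study's only success criterion. It settles the hypothesis, declares the model ready and leads to a tool for use in the rehabilitation center. A useful model should usually pass such a rule and an uninformative one should rarely pass.

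There are two weaknesses. F2 weights recall above precision, so at moderate or high prevalence a rule that labels everybody positive scores well without using any data. AUC, which has to do the remaining work, is a bare point estimate from what may be three to eight SUD participants. In a set that small a chance ordering often looks good, and a good model often looks bad.

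**Working it through.** **Sample size.** With the article's inputs (difference 2.54, SDs 1.6 and 3.21, two-sided 5%, 80% power):

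n = (1.6² + 3.21²)(1.96 + 0.84)² / 2.54² = 12.86 × 7.85 / 6.45 ≈ 15.7, so 16 per group (18 by Welch's t).

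The one-to-ten rule gives 40 in total, or 20 per group. Neither gives 25. That is a separate matter; 25 is used below as stated, because it fixes the fold size.

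**F2 of an all-positive rule.** F2 = 5PR/(4P + R). Calling everyone positive gives recall R = 1 and precision P = p, so F2 = 5p/(4p + 1). Setting this equal to 0.8 gives 5p = 3.2p + 0.8, so p = 4/9 = 44.4%.

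| Prevalence p | Where it comes from | All-positive F2 | Reaches 0.8? |
|---|---|---|---|
| 30% | illustration | 0.68 | no |
| 40% | illustration | 0.77 | no |
| 50% | SUD versus control, 1:1 (Sample Size) | 0.83 | yes |
| 60% | background relapse rate (Introduction), relapse taken as binary | 0.88 | yes |

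For the three relapse labels the value cannot be determined without a positive class or averaging rule.

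**AUC in one fold.** Under an uninformative ranking all orderings are equally likely, so the chance of AUC ≥0.80 is an exact count (Mann-Whitney null distribution). Assumptions: k from 3 to 10; for relapse, 25 SUD participants and a 60:40 split.

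| Comparison | k | Fold | P(AUC ≥0.80), no information |
|---|---|---|---|
| Relapse | 3 | 5 vs 3 | 7/56 = 12.5% |
| Relapse | 5 | 3 vs 2 | 2/10 = 20% |
| Relapse | 10 | 2 vs 1 | 1/3 = 33% |
| SUD vs control | 5 | 5 vs 5 | 19/252 = 7.5% |

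Simulating normally distributed scores in the 3-versus-2 fold, a model with true AUC 0.70 reaches the AUC threshold 46% of the time, true AUC 0.80 63%, and true AUC 0.90 83%.

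**Both criteria together, 3 versus 2.** Two of the ten orderings pass AUC. Suppose random scores are cut at 0.5, so that the number called positive is binomial (5, 0.5).
- Perfect ordering: F2 passes if three or more are called positive, probability 16/32.
- Ordering with AUC 5/6: F2 passes only if four or five are called positive, probability 6/32.
- Joint pass rate: (0.5 + 0.1875)/10 = 6.9%.

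If the cut-off is low enough to call everyone positive, F2 is 0.88 and always passes, so the joint rate is the full 20%.

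**Pooling every SUD participant (15 versus 10).** An uninformative ranking reaches 0.80 with probability 0.6%. For an observed AUC of 0.80 the Hanley-McNeil terms are 0.8/1.2 = 0.667 and 2(0.64)/1.8 = 0.711:

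SE = √{[0.16 + 14(0.667 − 0.64) + 9(0.711 − 0.64)]/150} = 0.088

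The 95% CI is 0.80 ± 1.96 × 0.088, about 0.63 to 0.97.

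**The case against.** A reader might infer that the rule cannot tell a useful model from a useless one, or that the F2 threshold screens out nothing. The document does not support either reading. The rule needs both criteria, and a constant all-positive classifier has AUC 0.5 and fails. In the 3-versus-2 fold an uninformative ranking reaches the AUC threshold 20% of the time against 63% for a true AUC of 0.80: poor separation, but not none. F2 does remove some chance passes unless the cut-off is low, and it is not trivial at prevalences below 44%. Precision and recall are also to be assessed, so an all-positive model would be noticed.

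The relapse figures rest on assumptions. The article has three relapse labels, its 60% is background rather than a design value, and k is open. The 7.5% for SUD versus control uses the design's own 1:1 ratio, but still assumes k=5.

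Sample size matters too. Twenty-five is a floor: with 50 SUD participants at k=5 (6 versus 4) the AUC figure is 5.7%, and with 100 (12 versus 8) it is 1.3%. The limitations section already concedes that small numbers may hurt performance. Against that, Results reports 18 SUD participants enrolled by June 2025, with recruitment open to January 2027.

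Finally, the article calls its scheme k-fold cross-validation, which ordinarily rotates the folds, and confidence intervals are often left to an analysis plan. That is fair as far as omissions go. But the text describes two folds drawn at random, "with 2 folds randomly selected: one for validation and another for testing", and final scores from that test set. What is challenged is the stated decision rule, not missing detail. The abstract's AUC-only wording may be condensation; it still differs from the three places that state both criteria.

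**Conclusion.** The point holds in a limited form. At the planned minimum size the rule discriminates weakly, for two reasons. F2 ≥0.8 lies at or below the all-positive score wherever prevalence is 44% or more, which includes the SUD-versus-control task at 1:1 (0.83). And the AUC, as written, comes from one small random fold of unfixed k.

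For an uninformative ranking, the chance of meeting the AUC threshold is 12.5% to 33% for relapse (25 SUD participants, 60:40 split, k from 3 to 10) and 7.5% for SUD versus control at k=5. Adding F2 brings the 3-versus-2 case to between about 7% and 20%, depending on the cut-off. These figures shrink with a larger sample, and pooling over 25 SUD participants takes the AUC figure to 0.6%. The F2 result for the three relapse labels is undetermined. The null probabilities are exact under their assumptions; Hanley-McNeil intervals are only approximate at these sizes.

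**What to change.** - **Data Preprocessing and Validation and Verification.** Rotate the test fold so that each participant is scored exactly once out of fold, with model selection and tuning confined to the training and validation folds. Compute the final AUC on the pooled out-of-fold predictions and report its 95% CI.
- **F2.** For each output, state the positive class or averaging and judge F2 against 5p/(4p + 1) at the observed prevalence. Alternatively, replace F2 with balanced accuracy, which is 0.5 for any constant rule.
- **Abstract.** Use the same criterion as in Validation and Verification, Predictive Model and the Discussion.

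Two tempting additions are not recommended. Requiring the lower AUC limit to exceed 0.5 does not bind here, since a pooled AUC of 0.80 already has a lower limit of about 0.63. Requiring a bootstrap lower limit for F2 above the all-positive value is too harsh. With 15 versus 10, a model with one missed relapse in 25 has F2 = 70/74 = 0.95 but a lower limit of about 0.82, below 0.88.

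The cost is more computation and a somewhat harder bar. Recruitment runs to January 2027, so the rule can still be changed before final testing.

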### Outcomes

#### Profiles

A total of 4 distinct subprofiles will be generated based on the results of the statistical analysis: (1) demographic, (2) psychological, (3) craving, and (4) digital biomarkers. These profiles will subsequently be integrated to create digital phenotypes for individuals with SUD.

#### Predictive Model

A predictive model will be developed to distinguish between healthy individuals and patients with SUD. In addition, the model will predict the duration of a rehabilitation therapeutic program and the length of sobriety adherence for individuals rehabilitated using the center’s methodology. A minimum performance threshold of AUC≥0.8 and F2≥0.8 has been established to evaluate the model as fully functional.

#### Graphical User Interface

As an outcome of this study, a graphical user interface will be developed using MATLAB to enable practical application of the predictive tool within the rehabilitation center where this research is being conducted. The graphical user interface will facilitate clinical use of the model and allow for further training and refinement, expanding its potential utility in similar settings.

### Ethical Considerations

This study has been approved by the Research, Ethics in Research and Biosafety committees of the Centro Universitario de Ciencias de la Salud, Universidad de Guadalajara (registry number 25-06; approval ID CI01225). This certifies that the research protocol adheres to the principles outlined in the Declaration of Helsinki of ethical research involving human participants, with a satisfactory quality and relevancy of the research.

Candidates will be provided with detailed materials in both written and digital formats for review before confirming their participation. All participants will be provided with an informed consent reviewed by the previously mentioned committees, signed by the participant, researchers, and two witnesses. Participants have the right to withdraw their consent at any time and may request the removal of their data from the study, in compliance with the Federal Law on Personal Data Protection and Article 16 of the Federal Constitution of the United States of Mexico [78,79].

All identifying participant information will be anonymized through a numeric ID system. Subsequently, the obtained data will be securely stored, either locked in a filing cabinet or in encrypted digital files and retained for a minimum of 5 years before being destroyed, as required by the Official Mexican Norm for Clinical Files (NOM-004-SSA3-2012) [80]. This information will only be accessible for purposes related to contact by the research group.

Participation in this study is entirely voluntary, and no financial incentives will be provided for joining or continuing in the study.

## Results

The study is supported by the Program for the Improvement of Working Conditions for Members of the SNII and SNCA (PROSNII U006EST), and APPAC-VII-CUCS-2025 for Article Publication Fees, from the University of Guadalajara. The research protocol was approved by the University of Guadalajara (reference CI-01225) in January 2025. Recruitment of patients with SUD and control participants will take place from January 2025 through January 2027. As of June 2025, we have enrolled 35 participants, 18 patients with SUD and 17 controls. Data obtained from the device, as well as psychological and demographic data at baseline assessments and at 3 months are at the labeling and preprocessing stage of the data analysis. Results are expected to be published by the summer of 2028.

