### Timeline

This study will include 2 types of observations: continuous passive monitoring and active surveys conducted at specific time points. Passive monitoring will occur continuously for 6 months in both groups, followed by an additional year for participants with SUD after their discharge from the treatment facility. Active surveys will be conducted at three time points: (1) baseline session or baseline, (2) 3 months after baseline, and (3) 6 months after baseline.

For digital monitoring purposes, smart bands provided to participants will be synchronized with a smartphone at the baseline session. Psychological assessment will be conducted within the first 15 days after baseline. Retesting will take place during the 15 days prior to the 6 months after baseline. Emotional reactions to cravings will be assessed at two points: (1) 3 months after baseline and (2) at 6 months after baseline (Figures 1A-1F).

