**Figure 5 figure5:**
[figure not shown]
Model’s possible outputs. These categories will be used as output labels of the predictive model and will allow the evaluation of the patterns detected from the input.

For the duration of the therapeutic process, the following labels will be used:

Timely rehabilitation: patients with SUD who complete the rehabilitation protocol within 7 months.Late rehabilitation: patients with SUD who complete the protocol in 7 months or longer.

Regarding relapse latency, the labels will include the following:

Early relapse: substance use occurring within the first 6 months post discharge.Late relapse: substance use occurring after 6 months but before the completion of 18 months post discharge.One-year maintenance: patients who have abstained from substance use at the end of the 18-month postrecovery period.

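### Recruitment to January 2027 and results by summer 2028 do not fit the 18-month post-discharge relapse label and leave almost no analysis time under the 12-month follow-up

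*Protocol article*

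**What the plan says.** - **Recruitment (Results):** "Recruitment of patients with SUD and control participants will take place from January 2025 through January 2027".
- **Publication (Results):** "Results are expected to be published by the summer of 2028". The article states no data lock, interim cut or restricted relapse cohort.
- **Label horizon (Output, labels under Figure 5):** early relapse is "substance use occurring within the first 6 months post discharge". Late relapse is "substance use occurring after 6 months but before the completion of 18 months post discharge". The one-year maintenance class is "patients who have abstained from substance use at the end of the 18-month postrecovery period".
- **Follow-up:** the Abstract (Methods) says "SUD participants will be monitored for a total of 18 months (6 months during rehabilitation, an additional 12 months post discharge". The Timeline section has six months of passive monitoring, "followed by an additional year for participants with SUD after their discharge from the treatment facility".
- **Length of stay:** it can exceed six months, since the late-rehabilitation class is "patients with SUD who complete the protocol in 7 months or longer". The Figure 1 caption starts the band after the first month of treatment for SUD patients.
- **After relapse:** Withdrawal Criteria and Data Exclusion end participation when an SUD patient relapses.

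**The concern.** The relapse-latency classes become known at different times. A relapse can be labelled on the day it is established, and the patient then leaves the study. Maintenance can be labelled only when the whole window has passed without use. If the calendar closes before a late enrollee's window does, he can be classified if he has relapsed and cannot be classified if he is still abstinent.

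An analysis held to the forecast date would then face two poor choices. Leaving out the late abstainers over-represents relapse. Counting them as maintained too early gives some future late relapsers the wrong class. These classes are both the training labels and the benchmark for the AUC and F2 thresholds of 0.8, so an outcome-dependent labelling rule would reach the model's headline performance.

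**Working it through.** **Inputs.** Last enrolment January 2027 and publication by summer 2028 (Results); about 6 months in rehabilitation (Abstract), or 7 and more (labels under Figure 5; an extra month also arises if enrolment is at admission and the band starts a month later); post-discharge window 12 months (Abstract, Timeline) or 18 months (labels); 18 SUD patients enrolled by June 2025 (Results); minimum 25 per group (Sample Size); 60% relapse rate (Introduction).

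**The plan's own total.** 6 + 12 = 18 months, as the Abstract states. The label horizon gives 6 + 18 = 24 months.

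**Completion date of a January 2027 enrollee** = enrolment + months to discharge + window:

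| Months to discharge | 12-month window | 18-month window |
|---|---|---|
| 6 | July 2028 | January 2029 |
| 7 | August 2028 | February 2029 |
| 8 | September 2028 | March 2029 |

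Taking summer 2028 as anything from 1 June to 22 September, the 18-month window with a 6-month stay ends about 4 to 8 months too late. The 12-month window ends during that season, or just after it for long stays. If the cut-off is 1 June 2028, even the 12-month window with a 6-month stay is missed by men enrolled after 1 December 2026.

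**Share incomplete, uniform accrual (assumed).** Count months from January 2025, with recruitment over 24 months and an assumed cut at month 44 (end of August 2028):

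share = (24 + months needed − 44) / 24, not below zero.

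- 18-month label: needed 24 gives 4/24 = 17%; needed 25 gives 5/24 = 21%.
- 12-month label: needed 18 or 19 gives −2 or −1, so 0%.

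Counting recruitment to the last day of January 2027 (25 months) changes 17–21% to 5/25 = 20% and 6/25 = 24%; the 12-month result stays at 0%.

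**Share incomplete, front-loaded accrual (assumed).** Take the 18 men as enrolled by about month 5.5 and the rest as evenly spread over the remaining 18.5 months. With the 18-month label, the last 4 to 5 months of recruitment are incomplete:

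- Final total 25: 7 × 4/18.5 = 1.5 men (6%) to 7 × 5/18.5 = 1.9 men (8%).
- Final total 40: 22 × 4/18.5 = 4.8 men (12%) to 22 × 5/18.5 = 5.9 men (15%).

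**Illustration of the bias.** Let f be the incomplete share, true relapse 60%, and half of the relapses among incomplete men seen by the cut (assumed). Relapse share is [(1−f)×0.6 + f×0.3] / [(1−f) + f×0.3] if incomplete abstainers are dropped, and (1−f)×0.6 + f×0.3 if they are called maintained.

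- f = 0.21: 0.537/0.853 = 63% if dropped; 54% if called maintained.
- f = 0.15: 0.555/0.895 = 62%; 56%.
- f = 0.06: 0.582/0.958 = 61%; 58%.

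At f = 0.21 in 25 men, the shift from 60% is 0.03 × 25, or about one man, in the first case and 0.06 × 25, or one to two men, in the second.

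**The case against.** The strongest reply has four parts.

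1. **The shorter horizon may be the intended one.** The Abstract, the Timeline section and the name of the one-year maintenance class all point to 12 months after discharge. On that reading a 6-month stay ends in July 2028 and nobody is incomplete at the end of August. This stands: the incompatibility depends on the 18-month label. But the labels state 18 months twice, for late relapse and for maintenance, and the shorter reading still leaves almost no time to analyse the last patients.
2. **A publication forecast is not a data lock.** This also stands. The ordinary result of an optimistic forecast is a later paper. The end-of-August cut used above is an assumption.
3. **No mislabelling is planned.** A reader might infer that the investigators intend to drop late abstainers or score them as maintained early. The article says neither, and early scoring would breach its own maintenance definition. The handling of incomplete follow-up may also sit in a document not shown. The bias is therefore conditional on keeping both dates.
4. **Uniform accrual is doubtful.** With 18 SUD patients by June 2025 against a minimum of 25, fewer late enrollees are likely than an even spread implies. Recruitment is nevertheless stated to stay open to January 2027 with an aim of more than 25 per group, so some late enrollees are planned.

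**Conclusion.** The concern holds in a limited form. As written, the recruitment period, the 18-month post-discharge label and the results date cannot all be kept. Under the 12-month follow-up they can nominally be kept, with roughly 0 to 2 months for everything after the last visit, and less for long stays.

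The damage is confined to the relapse-latency label, and it arises only if the analysis is cut to meet the forecast. The timely and late rehabilitation labels, and the comparison of SUD patients with controls, can still be scored for late enrollees.

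The affected share cannot be fixed from the article, because the final number, the accrual pattern and the cut date are not given. The range from 0% (12-month label) through 6–15% (front-loaded) to 17–21% (uniform) rests on the assumptions shown. The resulting shift in class proportions is modest, though it is systematic and easily avoided. It would go too far to say that the relapse outcome is already corrupted, or that late enrollees can never be scored: the documents support neither.

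**What to change.** First, reconcile the horizon in the Figure 5 labels with the follow-up in the Abstract and Timeline, so that one post-discharge window applies throughout. Then choose one of two options:

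- **Move the date.** Run the relapse analysis at last SUD discharge plus the full window, with time added for cleaning and modelling, and change the expected results date in the Results section. The cost is a later paper.
- **Keep the date.** Restrict the relapse model to men enrolled early enough to complete the window before the cut, with allowance for longer stays. Define this by enrolment date alone and apply it equally to relapsers and non-relapsers. With the 18-month label and an end-of-August 2028 cut, that means enrolment by about the end of August 2026 for 24 months needed, or the end of July 2026 for 25. Time reserved for analysis moves both dates earlier. Later enrollees still contribute to the duration labels and the control comparison. The cost is a slightly smaller relapse-model cohort.

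Either choice is best recorded before late enrollees' outcomes accrue.
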